#### Combined arm

The caregiver-child pair will start all three trial interventions, as outlined above.

The study team will provide the caregiver with an arm-specific booklet, providing an overview of their daily intervention; tools for recording adherence; 24-hour contact details for the study team; and their study clinic appointment dates. Prior to discharge, a study team member will collect household contact numbers, location and contact details of two neighbours, friends or relatives, and any plans for relocation.

#### Follow-up procedures

Children will attend a dedicated study clinic at weeks 2, 4, 6, 8 and 12 post-randomisation (with additional visits at 1, 3 and 5 weeks for the psychosocial and combined arms), with reimbursement provided for transport and time spent in the study clinic. Children are seen for additional clinical visits as determined by the trial team. At study visits, data will be collected on illness and hospitalisation (at study hospitals and other hospitals), and anthropometry will be conducted. Blood and stool will be collected at weeks 2 and 12, with repeat liver function testing at week 2 to identify possible hepatotoxicity from study drugs. RUTF will be supplied in all arms for at least 2 weeks, and then continued until the child achieves nutritional recovery (defined as a weight-for-height Z-score >–2, mid-upper arm circumference >12.5 cm, and oedema-free since the last study visit), using either standard RUTF or reformulated RUTF, depending on trial arm. If the child has not achieved nutritional recovery by week 12, or relapses before week 24 following nutritional recovery, s/he will be defined as reaching the primary outcome (failed nutritional recovery; see table 1); RUTF will be continued to a maximum of 16 weeks, and the child will be investigated for underlying causes. If the child achieves nutritional recovery but subsequently relapses, s/he will be defined as reaching the primary outcome, and RUTF will be restarted. In the antimicrobial arm, the study team will elicit any side effects, assess adherence by asking the caregiver to recall missed doses, and dispense medication at each visit to week 12. In all arms, the study team will check if children with HIV have started ART and cotrimoxazole; if not, ART initiation will be facilitated through referral to national programmes. In the psychosocial arm, the IF will undertake problem-solving therapy with the caregiver, deliver a module of behaviour-change material and undertake play activities with the child. After at least three individual sessions, the caregiver will be referred to a peer support group, which will meet weekly for six sessions. This group is led by an IF, with a focus on group problem-solving and income-generating activities. In the combined arm, all three interventions will be delivered at each study visit.

**Table 1 T1:** Trial outcomes

Primary outcome	
Death or first hospitalisation or failed nutritional recovery within 24 weeks post-randomisation	All-cause mortality or overnight admission to a health facility for any reason*, or failed nutritional recovery† within 24 weeks of randomisation

Secondary outcomes	
Change in weight-for-height Z-score between baseline and 24 weeks post-randomisation	Change in weight-for-height Z-score between baseline and 24 weeks post-randomisation according to age-appropriate and sex-appropriate WHO reference standards
Change in mid-upper arm circumference between baseline and 24 weeks post-randomisation	Change in size of mid-upper arm in centimetres between baseline and 24 weeks
Change in weight-for-age Z-score between baseline and 24 weeks post-randomisation	Change in weight-for-age Z-score between baseline and 24 weeks post-randomisation according to age-appropriate and sex-appropriate WHO reference standards
Change in height-for-age Z-score between baseline and 24 weeks post-randomisation	Change in height-for-age Z-score between baseline and 24 weeks post-randomisation according to age-appropriate and sex-appropriate WHO reference standards
Suspected or confirmed tuberculosis, pneumonia, diarrhoea or malaria through 24 weeks post-randomisation	Physician-diagnosed suspected or confirmed infection, as defined by WHO guidelines, between baseline and 24 weeks post-randomisation

Tertiary outcomes	
Change in anthropometry between baseline and 4 weeks post-randomisation	Change in WHZ, WAZ, HAZ and MUAC between baseline and 4 weeks post-randomisation
Change in anthropometry between baseline and 12 weeks post-randomisation	Change in WHZ, WAZ, HAZ and MUAC between baseline and 12 weeks post-randomisation
Change in caregiver mental health between baseline and 24 weeks post-randomisation	Change in Shona Symptom Questionnaire score (and proportion meeting cut-off score >8) between baseline and 24 weeks post-randomisation
Mechanistic laboratory endpoints	Exploratory endpoints based on comparing lipidomic, metabolomic, inflammatory and proteomic signatures between arms

* Includes cases where there was a clinical plan to hospitalise the child, which was refused by the caregiver.

† Defined as either: (i) persistent WHZ <–2 or MUAC <12.5 cm or bilateral pedal oedema at week 12; or (ii) WHZ <–2 or MUAC <12.5 cm or bilateral pedal oedema at any time between baseline and week 24 post-randomisation in a child who had previously recovered.

HAZ, height-for-age Z-score; MUAC, mid-upper arm circumference; WAZ, weight-for-age Z-score; WHZ, weight-for-height Z-score.

At 24 weeks post-randomisation, children will be seen for an endline research visit to collect primary and secondary outcome data, including repeat anthropometry. Children who fail to attend the 24-week visit will be seen at home, or caregivers will be contacted by phone, to collect intention-to-treat data on the primary outcome. No trial interventions will be provided beyond week 24. If children require ongoing care, they will be linked to local Ministry of Health services.

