#### Reformulated RUTF

Our goal is to reformulate RUTF to increase nutrient bioavailability and reduce metabolic stress and inflammation, thereby, improving nutritional recovery in children with SAM. Providing appropriate nutrients is critical for catch-up growth after SAM.^3^ Therapeutic feeding with RUTF occurs in the setting of profound metabolic dysregulation. During hospitalisation for SAM (especially in children with HIV), there is evidence of increased proteolysis, inflammation and dysregulated lipid metabolism, and a proteomic signature similar to metabolic syndrome.^18 19^ However, about 45%–60% of calories in RUTF are supplied in the form of long-chain triglycerides, which may contribute to the metabolic stress, and hence, to the poor outcomes among children with complicated SAM. The reformulated RUTF will supply some of the lipids in the form of medium-chain triglycerides (MCT), which may reduce metabolic stress, as MCTs are readily absorbed and metabolised by the liver. Evidence of higher gastric pH in children with SAM may reduce the ability to digest proteins^20^; hence, the reformulated product will provide amino acids in the form of pre-hydrolysed milk proteins to increase bioavailability. The product underwent research and development by the manufacturer (Nutriset, France), in collaboration with the trial investigators, to produce the final composition shown in online supplemental table 1. We conducted a pilot affective sensory test to explore the acceptability of the reformulated RUTF. A sachet of the reformulated RUTF was given to 25 children with complicated SAM ready to be discharged from hospital in Lusaka, Zambia. All children were eager to consume the reformulated RUTF, most finishing the sachet in less than 1 hour. Since we did not observe any sign of product rejection, the study team concluded that the RUTF was acceptable. A formal acceptability trial was not performed. The reformulated RUTF is expected to go into production in May 2025 and be introduced into the trial in July 2025.

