### Trial design

The trial protocol and case report forms are available at https://osf.io/824av/. Co-SAM is a five-arm, individually randomised clinical trial among children hospitalised with complicated SAM (figure 2). Children who have stabilised and started the transition to RUTF will be enrolled and randomised to one of the trial arms in hospital and will start the 12-week intervention prior to discharge. The trial will test the superiority of each intervention arm over a standard-of-care arm, using a 2:1:1:1:1 randomisation ratio in favour of standard-of-care. There will be no blinding or placebo as each trial arm has very different components. The trial is adaptive, meaning: (i) one country can start before another; (ii) trial arms will be introduced once each intervention is ready for testing; and (iii) an interim analysis will enable interventions which are unpromising to be dropped, based on pre-specified criteria.

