Ready-to-use therapeutic food is well tolerated and universal in guidelines globally for SAM.^3^ Although it contains peanuts and milk powder, there have been no reported cases of anaphylaxis; however, we will only enrol children who are already tolerating RUTF. The reformulated RUTF alters the composition of several nutrients but is not expected to affect the safety profile of the product. Our reformulation is grounded in observations of the distinct metabolic milieu in children with SAM,^18^ and it is likely that current recommended formulations are higher risk than the proposed reformulated product, which is designed to be more digestible and anti-inflammatory.

The psychosocial intervention is a low-risk intervention designed to provide play therapy, caregiver support and income-generating opportunities with peers. Screening for depression and anxiety may reveal caregivers with common mental disorders, but we will provide the best available, evidence-based intervention through the Friendship Bench. We will evaluate whether the time burden of this intervention for caregivers leads to unintended negative effects.

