#### Safety monitoring

All adverse events will be reported by research staff and reviewed by clinicians at each site for seriousness, relatedness, severity and expectedness. All serious adverse events will be reported to local regulators, the Data Monitoring and Ethics Committee and the trial sponsor.

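### Active side-effect questioning is described only alongside the antimicrobial drugs, so non-serious adverse event counts may not be comparable between arms in this open-label trial

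*Protocol article*

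**What the plan says.** All places are in the protocol article.

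- **Follow-up procedures, drug arm.** "In the antimicrobial arm, the study team will elicit any side effects". The same sentence adds adherence recall and dispensing, and sets the timing as each visit to week 12. The sentence after it assigns a different task, the check on HIV treatment, to every arm. The section says the combined arm gets all three interventions at each visit but does not mention side-effect questions there.
- **Follow-up procedures, all arms.** "At study visits, data will be collected on illness and hospitalisation (at study hospitals and other hospitals"), without restriction by arm.
- **Safety monitoring.** "All adverse events will be reported by research staff and reviewed by clinicians at each site for seriousness, relatedness, severity and expectedness". This also applies to every arm, but the section does not say how events are to be sought.
- **Table 1, secondary outcomes.** One outcome is "Suspected or confirmed tuberculosis, pneumonia, diarrhoea or malaria through 24 weeks post-randomisation", defined as "Physician-diagnosed suspected or confirmed infection, as defined by WHO guidelines, between baseline and 24 weeks post-randomisation".
- **Trial design.** "There will be no blinding or placebo as each trial arm has very different components".
- **Reformulated RUTF.** The product was tried as one sachet in each of 25 children. "A formal acceptability trial was not performed". Under Risks and benefits: "The reformulated RUTF alters the composition of several nutrients but is not expected to affect the safety profile of the product".

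**The concern.** How many minor adverse events are recorded depends on how they are asked about. A caregiver asked directly about side effects will report things that a caregiver asked only about illness may not mention. If the direct question is put only in arms that receive the antimicrobials, those arms may show more non-serious events than control with no true difference. With no blinding, neither staff nor caregivers are shielded from that expectation.

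Two further consequences are possible. Loose stools are a natural reply to a side-effect question, and the reply reaches the same clinical team that diagnoses suspected diarrhoea for the secondary infection outcome. Any such spill-over would count against the antimicrobial arm on an outcome close to its intended mechanism. Separately, the reformulated RUTF has little prior tolerability experience, and the article describes no enquiry directed at it, so the expectation of an unchanged safety profile would be tested with a less sensitive instrument than the drugs receive.

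**Working it through.** The point concerns how events are found. The plan gives no figure to reproduce, so the main check is a comparison of the text.

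**Step 1. What each arm is asked, as described**

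| Arm | Illness data at visits | Adverse events reported | Side effects actively elicited | Scheduled visits, weeks 1-12 |
|---|---|---|---|---|
| Control | yes | yes | not described | 5 |
| Antimicrobial | yes | yes | yes, to week 12 | 5 |
| Reformulated RUTF | yes | yes | not described | 5 |
| Psychosocial | yes | yes | not described | 8 |
| Combined | yes | yes | presumably, not stated | 8 |

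The visit counts are weeks 2, 4, 6, 8 and 12 (five), plus weeks 1, 3 and 5 in the psychosocial and combined arms (eight). Those extra contacts are a second reason to compare arms on common visits only.

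**Step 2. Which comparisons are exposed**

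Each arm is compared with control. For the antimicrobial and combined arms, the described enquiry differs from control, so adverse event counts can be biased. For the reformulated RUTF and psychosocial arms, the described questions match control. The elicitation sentence therefore does not bias those comparisons; for RUTF the loss is sensitivity.

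**Step 3. Illustration of size (assumed inputs)**

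The documents give neither a diarrhoea risk nor a capture rate. Assume the same true risk q in both arms, with capture c0 in control and c1 in the antimicrobial arm. Arm sizes of 422 and 211 are the minimum numbers under Final analysis.

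- Recorded risks: p0 = q × c0 and p1 = q × c1
- Odds ratio = [p1/(1 − p1)] / [p0/(1 − p0)]
- Expected z = (p1 − p0) / √[p0(1 − p0)/422 + p1(1 − p1)/211]

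Example with q = 0.30 and capture 0.80 v 0.90: p0 = 0.24 and p1 = 0.27. The odds ratio is (0.27/0.73)/(0.24/0.76) = 1.17, and z = 0.03/0.0370 = 0.81.

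| Capture, control v drug arm | q = 20%: OR (z) | q = 30%: OR (z) | q = 40%: OR (z) |
|---|---|---|---|
| 80% v 80% | 1.00 (0) | 1.00 (0) | 1.00 (0) |
| 80% v 85% | 1.08 (0.32) | 1.08 (0.41) | 1.09 (0.50) |
| 80% v 90% | 1.15 (0.63) | 1.17 (0.81) | 1.20 (1.00) |
| 70% v 90% | 1.35 (1.27) | 1.39 (1.65) | 1.45 (2.02) |

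For simple event counts the spurious ratio is c1/c0: 0.90/0.80 = 1.125, or 0.90/0.70 = 1.29.

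**Step 4. Why the diarrhoea figures lean high**

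The table applies the capture gap to all 24 weeks, but the prompt is described only to week 12. Take a control risk of 30% spread evenly. The 12-week risk is 1 − √0.70 = 0.163. For the 24-week recorded risk to rise by 20%, to 0.36, with weeks 12-24 unaffected, the 12-week figure must be 1 − 0.64/√0.70 = 0.235, and 0.235/0.163 = 1.44. So a 20% excess at 24 weeks needs 44% more children recorded by week 12. At a control risk of 50% the same steps give 0.434/0.293 = 1.48. Risk concentrated in the early weeks would lower these figures. If the four diagnoses are analysed as one composite, children who already have another diagnosis dilute the excess further.

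**The case against.** The strongest reply is that every arm already has a common route for recording events. Illness data are collected at study visits without restriction by arm, all adverse events are reported and reviewed by clinicians, and the infection outcome requires a physician diagnosis under WHO definitions. The side-effect sentence can be read as the list of extra tasks in an arm that dispenses drugs; it does not say that other arms go unasked. The case report forms are posted and may carry a common symptom list. Table 1 contains no between-arm safety outcome, and the process evaluation attends to unintended negative outcomes.

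Much of this stands, and it rules out several stronger readings that a reader might infer:

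- **That diarrhoea is ascertained unequally, as a fact.** The common illness route and the physician diagnosis mean that spill-over is only a risk.
- **That the gut effects of the reformulated RUTF are not asked about.** Illness collection and all-arm adverse event reporting would cover diarrhoea. What is absent from the description is a specific tolerability enquiry, which the posted forms may contain.
- **That safety cannot be compared across arms at all.** Reporting and clinician review apply to every arm.
- **That a spurious excess would cross the critical value of 1.904.** That value is a one-sided efficacy boundary. The article sets no harm test at it, so a z in the harm direction should not be judged against it.

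The reply does not dispose of the adverse event point. The section itself separates tasks for one arm from tasks for all arms and places elicitation among the former. Reporting all events in every arm does not make the enquiry equal when the method of finding them is unstated.

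**Conclusion.** The concern holds in a limited form. As described, active side-effect enquiry accompanies the antimicrobial drugs only, and no equivalent is stated for the control, reformulated RUTF or psychosocial arms. Non-serious adverse event counts in the drug arms are therefore open to upward bias relative to control. Spill-over into suspected diarrhoea is possible and would run against the antimicrobial arm, but it is not demonstrated.

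The size cannot be fixed from the documents. Under the assumed capture gaps above, spurious odds ratios for diarrhoea run from 1.08 to 1.45, with the upper end needing a 20-point gap sustained over all 24 weeks. The conclusion assumes that the article describes actual practice and that the combined arm is asked the same question as the antimicrobial arm. If the posted forms already put the same questions to all arms, only the wording of the article needs correcting. The primary outcome and the sample size are not at issue here.

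**What to change.** In Follow-up procedures, replace the arm-specific elicitation with one set of symptom and adverse event questions, including gastrointestinal symptoms. Ask them with identical wording in all five arms at the common visits (weeks 2, 4, 6, 8, 12 and 24). Put them before any arm-specific adherence or drug questions, which can stay arm-specific. State in Safety monitoring that between-arm comparisons of adverse events use these common-visit data, while reporting of all events, including serious ones, continues unchanged. No new rule is needed for the infection outcome, which already requires a WHO-defined physician diagnosis.

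Record the date on which the common questions take effect, so that children followed before it can be separated in the adverse event analysis. By 15 May 2025, 291 of the planned 1266 children (23%) had been enrolled, and the reformulated RUTF was expected in July 2025. A prompt change would therefore cover most of the trial and could cover all of the new product's use.

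The cost is a few more minutes per visit and more minor events recorded in the arms without drugs. No treatment changes.

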### Trial outcomes

Trial outcomes are listed in table 1.

### Laboratory analyses

Stool will be collected into sterile containers, then aliquoted for storage at −80°C. Whole blood will be centrifuged to separate plasma which will be aliquoted and stored at −80°C. The remaining cell pellet will be resuspended in red cell lysis buffer to deplete red cells and fix leucocytes, followed by a wash step, resuspension in freezing medium and aliquot storage at −80°C. Planned laboratory analyses on archived samples include targeted and untargeted lipidomics, metabolomics, proteomics and biomarker assays. These analyses aim to elucidate key biological pathways linked to poor post-discharge convalescence including metabolic, lipid and hormonal perturbations, inflammation and enteropathy, and the impact of the trial interventions on these mechanisms. Future substudies will capitalise on the biobank generated during the trial and perform exploratory analyses including the characterisation of cellular immune profiles before and after trial interventions.

### Data management

Study participants will be managed using an in-house, custom-developed secure database with pharmacy and laboratory management functions. Case report forms (CRFs) will be a combination of paper and electronic (eCRFs) forms captured using Research Data Capture (RedCap). All CRFs and eCRFs will have skip patterns, plausibility checks and will flag missing variables. All CRFs will be completed by clinical research staff and checked by data managers at each site. All identifiable data will be stored on paper in locked cabinets at each site accessible only to the study team and separate to CRFs containing de-identified data, which are labelled with unique study identifiers. Completed eCRFs will be uploaded to the trial server. Internal quality assurance systems will monitor data completion, data transfer and storage of CRFs regularly. A central team of data managers will provide automated queries and reviews of incoming data daily through a dashboard system across sites. Any missing or implausible data will be highlighted for site teams to resolve within stipulated timeframes.

### Sample size

For the primary analysis, a total sample size of 1266 participants across all three countries, with a final ratio of 2:1:1:1:1 in favour of standard-of-care, provides 80% power to detect a 30% reduction in the composite primary outcome of death or hospitalisation or failed nutritional recovery within 24 weeks, assuming a control arm event rate of 35% with overall one-sided alpha of 0.10 (ie, family-wise error),^32^ allowing for 5% loss to follow-up if all arms start at the same time. The control arm event rate was based on published data on mortality, readmission and nutritional recovery from the HOPE-SAM study^5 33^ in Zimbabwe and Zambia, and the Childhood Acute Illness and Nutrition network,^13 34^ which included sites in east Africa. Children who are enrolled but not randomised for any reason will be replaced.

### Statistical analysis

A pre-specified statistical analysis plan will be posted online at https://osf.io/824av/ prior to any analyses.

#### Interim analysis

One interim analysis will be undertaken once the following three conditions are achieved: (1) at least one active intervention arm reaches 106 participants; (2) the smallest active intervention arm reaches at least 50 participants; and (3) all four intervention arms are active. A logistic regression model accounting for country, age, sex and baseline oedema with indicators for each active treatment will be fitted on the composite primary outcome. If the test statistic falls below the lower (futility) bound of zero in an arm, indicating that there is no benefit of that arm over control, then that arm may be discontinued. Similarly, if the test statistic of an arm exceeds the upper (efficacy) bound (2.693), then that arm may be discontinued as it clearly suggests substantially lower mortality, hospitalisation or failed nutritional recovery than the control group. Active arms that have test statistics between the lower and upper bound will be continued, as they suggest potential benefit. The boundary estimates (0 and 2.693) have been calculated to control for the family-wise error. All decisions about dropping arms will be made in conjunction with the Data Monitoring and Ethics Committee, which comprises four independent members, and Trial Steering Committee, which comprises five independent members.

